### Sample size

Based on prior research [26, 28, 35], the magnitude of the effect size reflecting the degree of change in response to PASS vs TAU for service use and child outcomes (Objective 1) and care processes (Objective 2) is expected to be the 0.35 to 0.60 SD range. Based on prior research using a similar behavioral intervention [41], we assumed a standard deviation for a single observation = 0.50 and an autocorrelation = 0.3. Projecting an enrollment of 300 participants (150 per condition), and given an expected 20% attrition rate, we expect 240 participants will provide parent-report and child self-report data at baseline and at least one other data collection point. Using statistical methods described below, analytic models will achieve 85% power to detect an effect size as small as 0.30 SD. Given the challenges of collecting data from teachers related to the COVID-19 pandemic, the number of evaluable cases will be well below 240 (estimated to be 100). As such, analyses of teacher-report data will be exploratory. In addition, analyses of mediation (Objective 3) and subgroup effects (Objective 4) will be exploratory.

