#### Objective 3 (Explore whether changes in parenting practices, family empowerment, and perceptions of team-based care mediate the effect of intervention on child outcomes)

We will examine whether changes in parenting practices, family empowerment, or perceptions of team-based care mediate the effect of treatment (PASS, TAU) on child outcomes. We will employ the method proposed by Hayes for examining mediation effects with regression modeling approaches, utilizing PROCESS macro [64]. The models will reflect change scores in the mediators. To produce a precise estimate of mediation effects and properly account for the potential of regression to the mean, baseline measurement of the mediator will be included as a covariate [64]. In each analysis, we assess mediation by first estimating the effect of the intervention condition (PASS, TAU) on the child outcome at post-treatment, while controlling for the influence of the mediator and estimating the direct effect of the intervention on child outcomes without the mediator. The mediation effect is the difference in estimated intervention effects between the models. If the difference is not equal to zero, then there is evidence of mediation of the intervention on child outcomes.

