## Plan for Sensitivity Analyses to Determine Impact of Key Assumptions

### Objective 1 and objective 2

As a sensitivity analysis, we will use a Generalized Estimating Equation (GEE) approach to analyze Objectives 1 and 2. Like MMRM, GEE is based on regression techniques and uses all data obtained from each participant. Potential advantages of GEE are that it is suitable for both continuous and dichotomous outcomes, and it does not require the correct specification of the variance–covariance structure. Additionally, GEE can be used to model data with nested structures by accounting for the correlation among outcomes for individuals in the same aggregate.

#### Objective 3

We will explore a multiple mediator model using structural equation modelling. The multiple mediator model posits a path model for each additional mediator and estimates a separate effect for each mediator. The significance of the mediation effects can be tested using a Sobel test based on an asymptotic approximation to the distribution of the indirect mediation effects [68, 69]. However, because this test is sensitive to sample size, as an alternative sensitivity analysis for mediation analyses, we also plan to use a non-parametric bootstrapping approach. Additional methods based on simulations will also be considered [70, 71].

#### Objective 4

A simultaneous assessment of mediator–moderator effects will be examined. We will examine mediated-moderation effects and moderated-mediation effects using strategies outlined by Fairchild and MacKinnon [72] and Hayes [73]. These strategies extend the mediator and multiple mediator models described under Objective 3 by adding a moderator effect and an interaction between treatment by moderator effect to the main models. Tests of significance for the individual moderator, mediator and interaction effects can be conducted using tests of joint significance and similar bootstrapping methods as for mediation effects.

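### Objective 3's only written criterion for mediation is a non-zero difference between two estimates, tied to no test, interval or level, and the total effect is labelled the direct effect

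*Protocol article*

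**What the plan says.** In the protocol article, the a priori analysis section for Objective 3 names its framework: "We will employ the method proposed by Hayes for examining mediation effects with regression modeling approaches, utilizing PROCESS macro". Mediators enter as change scores, and "baseline measurement of the mediator will be included as a covariate". Two treatment effects on the child outcome are then estimated. One is adjusted for the mediator. The other is described as "estimating the direct effect of the intervention on child outcomes without the mediator". The section continues: "The mediation effect is the difference in estimated intervention effects between the models". Its closing criterion is: "If the difference is not equal to zero, then there is evidence of mediation of the intervention on child outcomes". No test, confidence interval or significance level is attached to it.

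Inference for mediation appears in the sensitivity-analysis section, also under Objective 3. In the paragraph on the multiple mediator model it says: "The significance of the mediation effects can be tested using a Sobel test". It adds that this test is sensitive to sample size and that "as an alternative sensitivity analysis for mediation analyses, we also plan to use a non-parametric bootstrapping approach".

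The Sample size section states that "analyses of mediation (Objective 3) and subgroup effects (Objective 4) will be exploratory".

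**The concern.** The definition of the mediation effect refers to estimated effects, and the next sentence asks only whether their difference is zero. Two estimated coefficients from continuous or many-valued scores essentially never coincide, so the sentence as written cannot return a negative answer.

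Elsewhere the protocol is more explicit. Objectives 1 and 2 carry a threshold of 0.025, and Objective 4 asks for a significant interaction. Objective 3 alone has a criterion with no reference to sampling error.

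The label is a second and separate slip. A treatment effect from a model that omits the mediator contains both the part that runs through the mediator and the part that does not, so it is the total effect. A report that followed the protocol's wording would present the total effect of PASS as its direct effect.

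At stake is the account of how PASS works, which is one of four stated objectives. The primary outcomes, their alpha and the sample size are not affected.

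**Working it through.** The protocol gives no figure for the mediation criterion, so there is none to reproduce. The check has three steps.

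**1. What the criterion tests.** Let c be the treatment coefficient from a regression of the outcome on treatment and baseline mediator, and c′ the coefficient when the mediator change is added. Let a be the effect of treatment on the mediator change, given baseline, and b the effect of the mediator change on the outcome in the second model. In least squares with the same children and covariates, c − c′ = a × b holds exactly for the estimates. The estimated difference is therefore zero only if an estimated a or b is exactly zero. An interval for a × b is an interval for the very difference that the protocol defines.

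**2. How the criterion behaves.**

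- From the Sample size section: 240 evaluable participants, taken as 120 per arm.
- From Objective 3: mediator as change score, baseline mediator as covariate.
- Assumed, not in the documents for this analysis: 5% two-sided level; mediator pre-post correlation 0.3; direct effect 0.3 residual SD; a = 0 or 0.35; b = 0 or 0.3.
- Model: M1 = 0.3·M0 + a·T + √(1 − 0.09)·e₁; D = M1 − M0; Y = 0.3·T + b·D + e₂.
- Runs: 3,000 for the written criterion and the Sobel test; 300, each with 300 resamples, for the percentile bootstrap.

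Share of runs that find mediation:

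| a | b | True mediation | Written criterion | Sobel, 5% | Bootstrap, 95% |
|---|---|---|---|---|---|
| 0 | 0 | none | 100% | 0.0% | 0.3% |
| 0.35 | 0 | none | 100% | 0.7% | 5.0% |
| 0 | 0.3 | none | 100% | 3.1% | 4.7% |
| 0.35 | 0.3 | 0.35 × 0.3 = 0.105 | 100% | 70% | 81% |

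The Monte Carlo standard error of the 5.0% bootstrap figure is √(0.05 × 0.95 / 300) = 1.3 percentage points, and that of the 81% figure is √(0.81 × 0.19 / 300) = 2.3 points. The 100% column follows from step 1 and does not depend on the assumed effects.

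The written criterion is met equally often with and without mediation, so meeting it carries no information. The two tools from the sensitivity section do separate the cases.

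**3. What the label does.** In the last row of the table, the true direct effect is c′ = 0.30 and the true total effect is c = 0.30 + 0.35 × 0.3 = 0.405. Under the protocol's wording, 0.405 would be reported as the direct effect. The size of the difference between the models, 0.105, is unchanged by the label.

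**The case against.** The best defence is that the sentence is shorthand for a hypothesis about the underlying difference. The surrounding text supports that reading. The same section commits to an established regression method for mediation. The sensitivity section speaks of testing the significance of mediation effects and plans a bootstrap, and under Objective 4 it refers back to bootstrapping for mediation effects. Authors who plan such tests hardly mean to call every non-zero estimate a mediator. The analysis is exploratory, and a condensed article may leave the type and level of an interval to an analysis plan that is not shown.

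Much of this stands. A reader might infer from the criterion that every mediator will be declared a mediator of every outcome, whatever the data show. The documents do not support that: even if the sentence were followed literally, the planned Sobel and bootstrap results would stand beside it. A reader might also infer that the direct and total effects have been swapped. They have not. One effect is mislabelled, and the adjusted effect is given no special name.

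The defence does not remove the point. The article did not leave the criterion to another document; it wrote one, and that one does not discriminate. Calling the bootstrap a sensitivity analysis implies that the main conclusion rests on something else, and the named method is not tied to any interval or level. Exploratory status relaxes expectations about power and multiplicity, but it does not justify a criterion that cannot fail. No reading of the criterion repairs the label.

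**Conclusion.** The concern holds in limited form. The only criterion written for the main Objective 3 analysis would, taken literally, be met by any mediator. The inference that could discriminate sits only under sensitivity analyses, with no level stated. The effect without the mediator is wrongly called direct.

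Severity is minor to moderate. The likely consequence is a mediation claim that is ambiguous or lacks error control, because a reader cannot tell which result the claim would rest on. The false-positive rates of about 0% to 5% for the Sobel test and the bootstrap, and their power of about 70% and 81%, rest on the assumed level, correlations and effect sizes. The failure of the literal criterion does not.

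**What to change.** Replace the criterion in Objective 3 with wording such as:

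*Mediation will be considered supported only if the non-parametric bootstrap confidence interval for the indirect effect, at the stated level, excludes zero. Models with and without the mediator will be fitted to the same children with the same other covariates. The effect from the model without the mediator is the total effect; the effect from the model with it is the direct effect.*

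Move the bootstrap from the sensitivity section into the main Objective 3 analysis; the Sobel test can remain as a sensitivity analysis. The team must choose and state the level. The check above used 95%; an interval at 97.5% would match the 0.025 threshold of Objectives 1 and 2. Keep the exploratory label.

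The cost is a few sentences. The bootstrap is already planned and no new data are needed. Fewer mediation claims will be made, and children without the mediator measurements drop out of both models.

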#### Objective 4 (Examining Heterogeneity of Treatment Effects; HTE)

Our general strategy is to determine whether the effect of treatment on outcomes varies as a function of baseline level of family resources, caregiver health literacy and stress, child medication status, and child mental health symptom severity at baseline, following the recommendations of Wang and Ware [65]. We will use a regression modeling approach with the outcome being change from baseline to post-treatment/follow-up, treatment groups being the independent variable, a subgrouping variable or covariate being the moderator tested, and the test of moderation being the interaction of treatment by the covariate. A significant interaction term indicates that treatment varies as a function of subgroup. For a subgroup variable with more than two levels (e.g., caregiver stress), the presence of a significant treatment by subgroup variable interaction will be followed by a series of post hoc analyses to conduct pairwise group comparisons. The *p* values for post hoc analyses will be used to calculate Bonferroni adjusted *p* values and false discovery rates (FDR) resulting from multiple comparisons [66, 67]. Given that HTE analyses will likely be underpowered, a consideration of Bonferroni adjusted values and FDR in the discussion of the heterogeneity of treatment effects will be informative.

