#### Clinical characteristics

Our team will explore whether clinical characteristics of the child at baseline, such as severity of ADHD, oppositional defiant disorder (ODD), and anxiety/depression symptoms assessed using the Vanderbilt scales, have a moderating influence on the effect of intervention on child outcomes.

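### The exploratory Objective 4 models use change from baseline and name no baseline-outcome covariate, which would cost about 35% of the information in most of them if r = 0.3

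*Protocol article*

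**What the plan says.** The Objective 4 section of the protocol article gives each element of the model a role. The outcome is a change score: "We will use a regression modeling approach with the outcome being change from baseline to post-treatment/follow-up". Treatment group is the independent variable, with "a subgrouping variable or covariate being the moderator tested, and the test of moderation being the interaction of treatment by the covariate". Neither the baseline value of the outcome nor the randomisation strata are mentioned, and neither is ruled out.

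The moderators are family resources, caregiver health literacy and stress, "child medication status, and child mental health symptom severity at baseline". The Clinical characteristics section spells out the last of these, "such as severity of ADHD, oppositional defiant disorder (ODD), and anxiety/depression symptoms assessed using the Vanderbilt scales". ODD and ADHD severity are therefore both moderators and outcomes.

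Elsewhere the article does name covariates. The Objective 1 model lists medication status and practice as fixed effects and allows further covariates. The Objective 3 section says that, to "properly account for the potential of regression to the mean, baseline measurement of the mediator will be included as a covariate".

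The Sample size section supplies the only correlation: "we assumed a standard deviation for a single observation = 0.50 and an autocorrelation = 0.3". It also calls Objective 4 exploratory, and the Objective 4 section itself expects low power.

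**The concern.** A change score subtracts the whole baseline value, whatever its correlation with the later score. When that correlation is below 0.5, subtraction adds more noise than it removes, and the analysis is less precise than one that ignores baseline. Entering baseline as a covariate lets the data choose the weight and, with equal variances at the two visits, gives a smaller residual variance at any correlation below 1.

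The article's own working value is 0.3, in the range where a plain change score does badly. Tests of treatment-by-moderator interaction are short of power from the start. For an exploratory objective the useful product is an interval estimate, and the width of that interval is what suffers. Real differences in effect by stress, literacy, resources or medication status become easier to miss. The Objective 4 regressions are separate from the mixed model, so changing the mixed model would not repair them.

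**Working it through.** **Inputs.** From Sample size: correlation 0.3, single-observation SD 0.50, and 240 evaluable children ("given an expected 20% attrition rate, we expect 240 participants will provide parent-report and child self-report data"), or 120 per arm at 1:1. The 240 have baseline and at least one later assessment, so any single visit has at most 240. Assumed here: equal variances at both visits; 0.3 read as the baseline-to-outcome correlation; and, for the illustration, a moderator that splits 50/50 (60 children per cell) and two-sided alpha 0.05. All effects are in units of the single-observation SD.

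**The plan's own power figure.** The article states "analytic models will achieve 85% power to detect an effect size as small as 0.30 SD". It gives no figure for Objective 4. A treatment difference averaged over three visits with first-order autoregressive correlation 0.3 comes close:
- variance of the mean = (3 + 4×0.3 + 2×0.09)/9 = 0.487
- SE = √(2×0.487/120) = 0.090
- power at 0.30 SD = 86.2% at two-sided 0.025, or 91.5% at 0.05.

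The match depends on choices the article does not state. A contrast of baseline-to-one-visit change, which is the form used in Objective 4, would have 39.1% power at 0.025 or 50.2% at 0.05 for the same 0.30 SD main effect. The 85% therefore says nothing about the Objective 4 models.

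**Residual variance at r = 0.3.**
- Change score, unadjusted: 2(1 − r) = 1.40
- Later score, baseline ignored: 1.00
- Baseline-adjusted: 1 − r² = 0.91
- Relative efficiency: 0.91/1.40 = (1 + r)/2 = 0.65, a 35% loss; SE ratio √(1.40/0.91) = 1.24.

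**Sensitivity to r.**

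| r | Loss, 1 − (1 + r)/2 |
|---|---|
| 0.3 | 35% |
| 0.5 | 25% |
| 0.7 | 15% |

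If 0.3 is instead the correlation between adjacent visits in an autoregressive pattern, r is 0.09 two visits apart and 0.027 three visits apart. The losses are then 45.5% and 48.7%.

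**Illustration for the interaction.** SE = √(4 × variance/60); detectable effect at 80% power = (1.96 + 0.84) × SE.

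| Model | SE | Detectable | Power at 0.50 SD | Power at 0.60 SD |
|---|---|---|---|---|
| Change, unadjusted | 0.306 | 0.86 SD | 37% | 50% |
| Baseline-adjusted | 0.246 | 0.69 SD | 53% | 68% |

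A simulation of the interaction estimate (4,000 runs, N = 240, r = 0.3) gave variances of 0.0922 and 0.0601, a ratio of 0.652, in agreement with the formula.

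**Where nothing is lost.** If continuous baseline ODD severity moderates the ODD outcome, baseline is already a regressor. Replacing the later score by the change score then only shifts the baseline coefficient by 1, and the interaction estimate is the same. The simulation gave 0.01577 for both variances.

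**The case against.** The strongest objection is that the article is silent rather than wrong. It describes a general strategy, does not call its list of terms complete, and a full analysis plan could add covariates. A reader might infer that baseline adjustment has been excluded; the text does not say so. What does stand is that the article fixes the change-score outcome and assigns every named term a role, while the Objective 1 and 3 sections name covariates where they are wanted. That makes accidental omission less likely without excluding it.

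Other readings also go further than the documents allow:

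- **Strata.** A reader might attribute part of the 35% to leaving out practice and medication status. All of it comes from the baseline term, and the documents give no input for sizing a gain from the strata. In the medication model one stratification factor is already present as the moderator.
- **Every Objective 4 model.** The exception for ODD or ADHD severity moderating its own outcome is real, though narrow. It does not reach resources, stress, literacy, medication status, anxiety/depression, or severity moderating a different outcome such as homework problems.
- **Bias.** The reference to regression to the mean in Objective 3 might suggest a biased estimate here. That adjustment concerns a mediator, which is not randomised. The randomised treatment-by-moderator contrast is unbiased with or without baseline.
- **A flaw special to Objective 4.** With complete data, a mixed model that treats baseline as an unconstrained time point gives the same change contrast. The choice is thus in line with the rest of the plan, which reports differences in change. This explains the choice but does not make it efficient.

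It is also fair to say that 0.3 was stated for the Objective 1 and 2 power calculation, that 0.60 SD is the top of the range expected for treatment effects rather than interactions, and that the even split is an assumption. The size is therefore conditional; the direction is not, for any correlation below 1 under equal variances.

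**Conclusion.** The point holds as a recommended, inexpensive gain in precision for an exploratory objective. As written, the Objective 4 regressions use change from baseline with no named baseline-outcome covariate. If they are run that way and the baseline-to-outcome correlation is 0.3, about 35% of the information is lost in the models where baseline is not already the continuous moderator, and standard errors are 24% larger. At correlations of 0.5 and 0.7 the loss is 25% and 15%. The detectable interactions of 0.86 and 0.69 SD are illustrative and rest on an even moderator split and no more than 240 children. No bias or error-rate inflation follows, and no primary conclusion depends on these models.

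**What to change.** In the Objective 4 section, state that each model includes the baseline score of the outcome being analysed, unless that score is already in the model as the continuous moderator. Add practice and baseline medication status so that the model is consistent with Objective 1, entering medication status once only when it is the moderator. Change may remain the outcome: with baseline as a covariate, change and later score give the same interaction estimate.

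The cost is a sentence of wording and no new data. At most eight degrees of freedom are used (one for baseline, six for seven practices, one for medication status) out of about 240.

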#### Assessment of intervention fidelity

PASS sessions will be audio recorded to enable our team to examine intervention content fidelity. The PASS treatment manual includes two standard sessions (sessions one and two) that are always presented and a variable number of additional sessions (sessions 3 +) that can be selected depending on presenting concern and family need or preference. Checklists reflecting session components will be used to assess content fidelity. Up to four sessions will be selected for content coding for each participant in the PASS condition. Sessions one and two will always be coded. One randomly selected session from sessions 3–5 and another from sessions 6 + will be selected for coding. Independent coders who have previous training in psychosocial treatment of ADHD will code all selected tapes and 25% of tapes will be double-coded to establish inter-rater reliability. An intraclass correlation coefficient (ICC) of at least 0.6 will indicate acceptable agreement [37].

The Community Health Partner will complete a survey after each encounter with a caregiver that provides information on topics discussed, barriers, stressors, strategies to address barriers and stressors, caregiver perceptions of care, resources, and the support process included in the call. To monitor Community Health Partner process fidelity, we will use a self-evaluation checklist completed by Community Health Partners after contact with a family. Process items include establishing trust, listening attentively, and re-directing tangential comments [38].

#### Measures of outcomes – examined for objective 1

Outcomes are differentiated into primary versus secondary and informant providing data (parent, teacher, child self-report). Two parent-report measures (ratings of homework performance and behavior compliance) have been identified as primary because these are a major focus of the PASS intervention. Teacher-report measures are secondary because of challenges obtaining these data due in large part to the burden placed on schools. Child self-report measures are secondary because some children, especially those under the age of 8, may have difficulty understanding and responding to these measures.

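### Objective 4 corrects for multiplicity only in post hoc pairwise comparisons, while the interaction tests that carry the subgroup claims have no stated alpha or correction

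*Protocol article*

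**What the plan says.** The relevant text is the Objective 4 section on heterogeneity of treatment effects in the protocol article.

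- **Moderators.** The effect of treatment is to be examined by "baseline level of family resources, caregiver health literacy and stress, child medication status, and child mental health symptom severity at baseline". The Clinical characteristics section divides symptom severity further, "such as severity of ADHD, oppositional defiant disorder (ODD), and anxiety/depression symptoms".
- **Model.** A regression "with the outcome being change from baseline to post-treatment/follow-up", with treatment, the moderator (a subgrouping variable or a covariate) and their interaction. No other term is listed.
- **Decision rule.** "A significant interaction term indicates that treatment varies as a function of subgroup". No alpha is given.
- **Next step.** "For a subgroup variable with more than two levels (e.g., caregiver stress"), a significant "interaction will be followed by a series of post hoc analyses to conduct pairwise group comparisons".
- **Correction.** The p "values for post hoc analyses will be used to calculate Bonferroni adjusted" values and false discovery rates. The section then says that these adjusted values will inform the discussion of heterogeneity, because the analyses are likely to lack power.

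Elsewhere, the Sample size section labels the subgroup analyses exploratory. The outcome section states that "Two parent-report measures (ratings of homework performance and behavior compliance) have been identified as primary". Objectives 1 and 2 are tested at 0.025, apart from the teacher measures, which are tested at 0.05.

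**The concern.** The claim that treatment works differently in a subgroup is made at the interaction test. The pairwise comparisons only describe where the difference lies once that claim has been made. Adjusting the comparisons alone leaves the false-claim rate of the first step untouched.

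Some moderators never reach the corrected step. Medication status (yes or no) has two levels, and a moderator entered as a continuous covariate has no levels to compare. Neither produces a post hoc p value, so neither receives any correction. The section's own aim, to discuss heterogeneity in the light of adjusted values, cannot be met for the tests that matter most.

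Two features of the model add to this. Grouping a scale score such as perceived stress discards information, and an unadjusted change score is noisier than a baseline-adjusted outcome. Both work against an analysis that the article already expects to lack power. At stake is a spurious differential effect reported for a vulnerable group of families, or a real one missed.

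**Working it through.** The article gives no number of tests, alpha or error rate for Objective 4, so there is no stated figure to reproduce. The counts below are derived.

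**1. Number of interaction tests** (moderators × outcomes × time points)

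- Moderators: 5 as listed under Objective 4 (family resources, health literacy, stress, medication status, symptom severity). This becomes 7 if symptom severity is split into ADHD, ODD and anxiety/depression, and 9 if family resources is also split into income/poverty, financial strain and education, which the Sociodemographic factors section measures separately.
- Outcomes: 2 primary, both parent-reported.
- Time points: 2 (post-treatment and follow-up).

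This gives 5 × 2 × 2 = 20, 7 × 2 × 2 = 28, or 9 × 2 × 2 = 36.

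**2. Chance of at least one false positive**, 1 − (1 − α)^k, and expected number, α × k, if all nulls are true and the tests are independent. Both alphas are assumptions.

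| Tests k | α = 0.05: chance | expected | α = 0.025: chance | expected |
|---|---|---|---|---|
| 20 | 1 − 0.95^20 = 64% | 1.0 | 1 − 0.975^20 = 40% | 0.5 |
| 28 | 76% | 1.4 | 51% | 0.7 |
| 36 | 84% | 1.8 | 60% | 0.9 |

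The narrowest reading, five moderators at a single time point, gives 5 × 2 = 10 tests: 40% at 0.05 and 22% at 0.025. At the other end, nine parent- or child-reported outcomes (homework, ODD, inattention, hyperactivity-impulsivity, parent-rated academic proficiency, and peer relationships and life satisfaction from two informants each) at two time points give 90 to 162 tests, and 99% or more at 0.05.

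The same outcome at two visits, and overlapping socioeconomic or symptom moderators, give positively correlated tests. The independence figures are therefore upper guides for each k. The expected counts do not depend on independence.

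**3. Cost of an unadjusted change score.** Inputs: autocorrelation r = 0.3 from the Sample size section, and equal variances at both visits (assumption), in units of SD².

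- Change score: 2(1 − r) = 2 × 0.7 = 1.40
- Baseline-adjusted outcome: 1 − r² = 1 − 0.09 = 0.91
- Ratio: 1.40 / 0.91 = 1.54, or about 54% more residual variance.

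One pairing is an exception: where baseline ODD severity is the moderator and the parent ODD score is the outcome, the moderator is close to the baseline outcome itself.

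**4. What correction does to power.** For two equal subgroups and N = 240 there are 60 per arm in each, so the SE of the interaction is √(2/60 + 2/60) = 0.258 SD. An interaction of 0.30 SD has power Φ(0.30/0.258 − 1.96), about 21%, at 0.05. At the Bonferroni level 0.05/20 = 0.0025 it is about 3%. For 0.60 SD the figures are about 64% and 24%.

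**The case against.** The strongest reply is that Objective 4 is labelled exploratory, its moderators are named in advance, it uses formal interaction tests rather than within-subgroup p values, and the article warns of low power. Unadjusted interaction tests are a common and defensible choice under that label. This stands, and it limits the weight of the point: no primary conclusion is affected. It does not rescue the rule as written, because the article chooses to correct for multiplicity and places the correction where it cannot reach the claim. The decision sentence is also worded more firmly than an exploratory test allows.

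It can also be said that the error rates rest on an assumed alpha, a chosen count and independence. That is correct, and is why a range is given. If the 0.025 used for Objectives 1 and 2 also applies here, the lower range holds.

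A reader might go further and infer two things that the document does not support:

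- **That incomplete cases are dropped.** No section specifies a complete-case analysis. The missing-data section says that maximum likelihood and multiple imputation will be considered, without limiting this to any objective, and imputed data can feed a change-score regression.
- **That continuous moderators in general are cut into groups.** Levels are shown only for caregiver stress, as an example and without cut-points. The model expressly allows a covariate as the moderator, so health literacy and symptom scores may well stay continuous.

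Finally, a change-score regression is a legitimate estimator in a randomised trial, and a condensed article may leave its covariates to the full plan. The baseline point therefore concerns precision, not bias in the treatment comparison, and rests on the terms that the section lists.

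**Conclusion.** The point holds in a limited form. The Objective 4 correction is attached to the wrong set of p values: interaction tests decide whether heterogeneity is claimed, and they have no stated alpha or adjustment. On the two primary outcomes at two time points there are 20 to 36 such tests. The chance of at least one false positive is about 64–84% at 0.05 or 40–60% at 0.025, assuming independence and no true moderation. The 84% is the top of this range and should not be read as the trial's actual error rate.

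As secondary points, the one scale score shown with levels, perceived stress, would lose information if grouped, and the listed regression carries about 54% more residual variance than a baseline-adjusted one under r = 0.3 and equal variances. This should be corrected, but it bears on exploratory findings only.

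**What to change.** Reword Objective 4 as follows.

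1. List the moderators, outcomes and time points to be tested, give the resulting number of interaction tests, and state the alpha.
2. Apply FDR to the full set of interaction p values, including those for two-level and continuous moderators. Report raw and adjusted values and describe the results as exploratory. FDR is preferable to Bonferroni here, given the power in step 4 of the working.
3. Keep perceived stress, and any other scale score, continuous in the test, with subgroup displays for illustration only.
4. Adjust the moderation model for the baseline outcome and the stratification factors (practice and medication status), or estimate moderation within the MMRM already planned for Objective 1.
5. Soften the decision sentence, so that a significant interaction suggests heterogeneity rather than establishes it.

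The cost is a change of analysis wording and slightly stricter exploratory claims. No data collection, sample size or primary analysis changes.
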